### 9.3 ANALYSIS SETS

All patients who were enrolled into the study are included in the main analyses. In fact, the primary and secondary outcome measures are analyzed according to the intention-to-treat principle. In addition, a modified intention-to-treat analysis is planned, excluding patients with a dose interruption in case of an adverse event or discontinuation of study treatment for other reasons, such as use of prohibited medication (see section 6.6). A complete case analysis is performed as sensitivity analysis.

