| Analysis of efficacy:                                 | 
The primary analyses of efficacy endpoints will follow the intention-to-treat principle including all patients who are enrolled into the study. In addition, a modified intention-to-treat analysis will be conducted excluding patients with a dose interruption due to adverse events.
 
Primary endpoint of the core study period
 
The primary endpoint is the reduction of serum anti-dsDNA antibody titers after 8 repeated weekly injections of daratumumab at Week 12, i.e. 4 weeks after the last daratumumab injection, compared to baseline.
 
Primary endpoint of the LTE observational period
 
Safety, will be investigated by reporting the proportion of participants with treatment emergent adverse events (TEAE) by severity and SAEs through EOS.
 
Secondary endpoints of the core study and LTE observational period
 
 
1. Safety, will be investigated by reporting the proportion of participants with treatment emergent adverse events (TEAE) by severity and SAEs through EOS.
 
2. To investigate the effect of daratumumab on serologic changes, the following secondary endpoints are defined: 
 
• Change from baseline in serum levels of anti-dsDNA antibodies, immunoglobulins (IgM, IgG and IgA), antinuclear antibodies (ANA) and extractable antinuclear antibodies (ENA), such as anti-Smith, anti-Ro (SSA), anti-La (SSB), anti-ribonucleoprotein (RNP) and anti-phospholipid antibodies, rheumatoid factor (RF) and anti-citrullinated peptide antibodies (ACPA) (if present) by visit.
 
• Change from baseline in serum complement factors for C3 and C4 by visit.
 
• Change from Baseline in levels of protective vaccine-induced serum antibody titers for Tetanus toxoid, Diphtheria and Measles by visit.
 
 
 
3. To evaluate whether daratumumab treatment is associated with clinical efficacy and glucocorticoid sparing, the following secondary outcome measures will be analyzed: 
 
• Proportion of subjects with a SLE responder index of 4 (SRI-4); Time frame: Week 12.
 
 
 
 |

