#### **Infection or predisposition to infection**

15. has a history of, or ongoing, chronic or recurrent infection, including but not limited to, chronic renal infection, chronic chest infection (e.g. bronchiectasis), sinusitis, recurrent urinary tract infection (e.g. recurrent pyelonephritis), an open, draining, or infected skin wound, or an ulcer.
16. Evidence of latent tuberculosis (as documented by a positive QuantiFERON-TB test at screening, no findings on medical history or clinical examination consistent with active tuberculosis, and a normal chest radiograph) except for participants that are willing to complete at least 4 weeks of anti-tuberculosis therapy as per WHO or national guidelines prior to randomization and agree to complete the remainder of treatment while in the study.
17. has or has had a serious infection (e.g. sepsis, pneumonia or pyelonephritis) or has been hospitalized or received IV antibiotics for a serious infection during the 3 months prior to consent.
18. Ongoing infection (requiring antibiotic treatment or fever > 38°C), including known HIV, active or chronic hepatitis B or hepatitis C.
19. has experienced a recent single dermatomal herpes zoster eruption within the past 6 months, or has a history of disseminated forms of zoster within the past 2 years prior to Screening.
20. has a history of hepatitis B surface antigen (HBsAg) or hepatitis C antibody (anti-HCV) positive, or other clinically active liver disease, or tests positive for HbsAg or anti-HCV at Screening.
21. has a history of human immunodeficiency virus (HIV) antibody positive, or tests positive for HIV at Screening.
22. have had an opportunistic infection (e.g. pneumocystis, aspergillosis, mycobacterium avium complex).
23. has a SARS-CoV-2 Infection at screening or baseline, confirmed by a PCR test (a rapid test is mandatory before each visit; if this test is positive, then a PCR test must be performed).

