## 9 STATISTICAL METHODS

### 9.1 SUBJECT INFORMATION

#### 9.1.1 DEMOGRAPHICS AND BASELINE CHARACTERISTICS

For all subjects who receive at least 1 dose of daratumumab, descriptive statistics on demographics and baseline disease characteristics will be provided. Descriptive statistics (mean, standard deviation, median, and range) will be provided for the subjects' age, weight, height, anti-dsDNA antibody titers, SLEDAI-2K score, PGA score, CLASI, CDAI, SF-36 and FACIT-Fatigue. Subject sex, race, concomitant medication use, number of BILAG A or BILAG B criteria, positivity for ANA, anti-dsDNA antibodies, or other autoantibodies, number with low complement C3 or C4 levels will be summarized as frequency distributions.

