### 9.1.2 DISPOSITION INFORMATION

Disposition information will be based on all subjects who receive at least 1 dose of daratumumab. The number of subjects who discontinued daratumumab and the reason for discontinuation as well as those who terminated the study and reason for termination will be summarized.

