### 9.4 MISSING VALUES

Missing values in primary and secondary outcome measures will be replaced by the last known value of any previous assessment (LOCF principle) for the primary analyses. Missing data for safety endpoints will not be replaced.

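### The main efficacy set is all enrolled patients with no dosing condition, while baseline and disposition tables use dosed patients; an enrolled but never-dosed patient would count as a zero change

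*Protocol*

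**What the plan says.** Section 9.3 sets the main population: "All patients who were enrolled into the study are included in the main analyses". It applies this to the primary and secondary outcome measures. The synopsis says the same: "The primary analyses of efficacy endpoints will follow the intention-to-treat principle including all patients who are enrolled into the study". Neither place adds a dosing condition.

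The descriptive sections use another population. Section 9.1.1: "For all subjects who receive at least 1 dose of daratumumab, descriptive statistics on demographics and baseline disease characteristics will be provided". Section 9.1.2: "Disposition information will be based on all subjects who receive at least 1 dose of daratumumab".

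Section 9.4 deals with gaps in efficacy data: "Missing values in primary and secondary outcome measures will be replaced by the last known value of any previous assessment (LOCF principle"). Two further analyses are named in 9.3. In one, "a modified intention-to-treat analysis is planned, excluding patients with a dose interruption in case of an adverse event or discontinuation of study treatment"; the other is described as "A complete case analysis is performed as sensitivity analysis". Section 9.5.1 reports medians at baseline and Week 12 and the median change with a 95% interval, without naming the interval method.

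**The concern.** The trial has one arm and no randomisation, so an all-enrolled set protects no comparison. The primary endpoint (section 3.2.1) is the change after a course of injections, and a patient who received none carries no information on it.

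If such a patient exists, the written rules have four consequences:

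- The missing Week 12 titre is filled with the pre-dose titre, so the change is exactly zero.
- A carried-forward SLEDAI-2K score cannot show the 4-point reduction that SRI-4 requires, so the patient is a non-responder.
- The patient counts in the efficacy results but is absent from the disposition table, so a reader cannot reconcile the denominators. The baseline median titre in 9.1.1 and the one in 9.5.1 would also come from different sets.
- The proportion of participants with treatment-emergent adverse events is secondary endpoint 1 (section 3.2.3). Read literally, 9.3 puts the unexposed patient in its denominator.

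The modified set does not clearly remove such a patient, since it names interruption and discontinuation but not failure to start. With only 10 patients, one structural zero is visible in the results.

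**Working it through.** **Inputs.** N = 10, mean change -250 IE/ml and SD 121 (section 9.2, from two patients). Normality of the change is an assumption made here. The number never dosed, k, is not given in the protocol; k = 0, 1 and 2 are shown.

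**The plan's own figure.** Effect size 250/121 = 2.07, stated as 2.1. A noncentral t calculation with the usual efficiency adjustment for the signed-rank test (3/π) gives power 0.74 at n = 4 and 0.90 at n = 5 with d = 2.066. So 5 is the smallest size with 80% power, and 5/(1 - 0.5) = 10. The plan's numbers reproduce, and this point does not affect them.

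**Mean change.** With k zeros among 10, the mean is -250 × (10 - k)/10: -225 for k = 1 and -200 for k = 2.

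**Median change.** The median of 10 is the average of the 5th and 6th ordered values. The zeros sit almost always at the top, so these are the 5th and 6th ordered values among the dosed patients.

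- k = 1: the expected standard normal order statistics for n = 9 are 0 and 0.275. Their average is 0.137, and -250 + 121 × 0.137 ≈ -233.
- k = 2: for n = 8 they are 0.153 and 0.473. Their average is 0.313, and -250 + 121 × 0.313 ≈ -212.

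Simulation of 100,000 trials agrees:

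| Never dosed among 10 | Expected median, all enrolled | Expected median, dosed only |
|---|---|---|
| 0 | -250 | -250 |
| 1 | -233 | -250 |
| 2 | -212 | -250 |

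The shifts are 17/250 = 7% and 38/250 = 15%.

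**Response proportion (illustration).** Five responders among nine dosed patients is 5/9 = 56%; with one never-dosed patient in the denominator it is 5/10 = 50%. With two, 5/8 = 62.5% becomes 50%.

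**Confidence interval.** The chance that one dosed patient's change is zero or above is Φ(-2.066) = 0.0194. The chance that the interval for 10 enrolled patients reaches zero depends on the method:

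| Interval method | k = 1 | k = 2 |
|---|---|---|
| Order statistics, ranks 2 to 9 (coverage 97.9%) | 1 - 0.9806^9 ≈ 16% | 100%, because the 9th value is then never below zero |
| Signed-rank (Walsh averages), simulated | about 0.1% | about 1% |

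The first method is for the median itself. The second is for the pseudomedian and corresponds to the test named in 9.2. The protocol chooses neither.

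**Adverse events.** A simple proportion with one never-dosed patient has 10 in place of 9 in its denominator. The rate per 10 treatment months in 9.5.2 does not change, because that patient adds no treatment months.

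**The case against.** The strongest reply is that the case hardly arises. Section 5.1 requires all criteria to be met for a patient to be enrolled, and some can only be settled at dosing, such as the urine pregnancy test before the first dose. Section 5.2 lists a patient who "has a SARS-CoV-2 Infection at screening or baseline, confirmed by a PCR test" as excluded. The schedule puts the second eligibility check and the first injection at the same Day 0 visit, and section 13.3 keeps a screening log separate from the enrollment log. This largely stands. A reader might infer that a cold or a positive PCR at baseline routinely produces enrolled but untreated patients; the text reads more naturally as making these screen failures. What remains is mainly a patient who is confirmed eligible and then not injected, and the protocol does not expressly define enrolment to rule this out.

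Three further replies have weight. The complete case analysis would drop a patient with no Week 12 value, though only as a sensitivity analysis. The analysis is exploratory, and a zero works against the drug. The zero is exact only if no later sample exists; the early termination visit in 8.3 includes anti-dsDNA serology and would give an untreated value instead.

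Two stronger readings should be resisted. One is that two never-dosed patients make the interval reach zero whatever the drug does. That is true of the order-statistic interval and false of the signed-rank interval, and 9.5.1 names no method. The other is that adverse event incidence is understated throughout. Section 9.5.2 gives rates per treatment months and 9.1.4 reports the number exposed, so only the simple proportion could be diluted.

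**Conclusion.** The mismatch between 9.3 with the synopsis and 9.1.1 with 9.1.2 is real, and the zero change follows from 9.4. Its practical weight is small. It needs an enrolled patient who was never dosed and has no later sample, which should be rare, and it has no effect otherwise.

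If one such patient occurs, the expected median change is understated by about 17 IE/ml; if two occur, by about 38. These sizes rest on the planning mean and SD from two patients and on assumed normality. Response proportions fall by the ratio of dosed to enrolled patients. No general statement about the confidence interval is supported. This is a worthwhile clarification at no cost, and it does not threaten the trial's conclusions.

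**What to change.** In section 9.3 and the synopsis, define the main efficacy set as all patients who received at least one dose of daratumumab, the set already used in 9.1.1 and 9.1.2. State that the same set is the denominator for proportions with treatment-emergent adverse events. In 9.1.2, list any enrolled but never-dosed patients, with the reason, so that the counts reconcile.

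The cost is a few sentences. No patient, visit or data item is added, and because the trial is uncontrolled no randomised comparison is given up. The change should be made before the outcome data are analysed.

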## 6.6 PROHIBITED THERAPIES

Use of additional immunosuppressants or immunomodulators, other than those explicitly allowed in the inclusion/exclusion criteria are prohibited including, but not limited to, the following:

- Agents targeted at reducing TNF (e.g. infliximab, golimumab, certolizumab pegol, etanercept, and adalimumab)
- B-cell depleting agents (e.g. rituximab, obinutuzumab or ocrelizumab)
- Interleukin-1 inhibitors (e.g. canakinumab)
- IL-1 receptor antagonist (e.g. anakinra)
- Interleukin-2 inhibitors or exogenous IL-2 therapy
- Tocilizumab or any other biologic targeting IL-6 or IL-6 receptor
- Tofacitinib, baricitinib, filgotinib, upadacitinib or any other janus kinase (JAK) inhibitors
- Abatacept
- Anti-IL-17 agents (e.g. secukinumab or ixekizumab)
- Anti-IL-23 agents (e.g. guselkumab)
- Leflunomide
- Tacrolimus or other immunomodulatory oral or topical preparations
- Thalidomide or lenalidomide
- Dapsone

Use of cytotoxic drugs is prohibited including, but not limited to, cyclophosphamide, chlorambucil, nitrogen mustard, or other alkylating agents. Multiple administrations of high doses of oral glucocorticoids (average daily dose  $\geq 20$  mg), or initiation of high potency topical glucocorticoids, are prohibited during the study. Sulfa-based antibiotics, where reasonable, should generally be avoided. The use of complementary therapies (e.g. herbs, ointments, traditional Chinese medicine, and acupuncture) that have the potential to activate or inhibit the immune system is prohibited. In addition, use of complementary therapies that have the potential to interact with antithrombotic agents is prohibited in those taking antithrombotic agents. The use of other complementary therapies is strongly discouraged; in individual cases, use may be permitted following discussion with the study sponsor and/or medical monitor.

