### 7.2.3 SELENA-SLEDAI FLARE INDEX

One key secondary objective is to assess the flare rate in daratumumab treated patients. The corresponding secondary endpoint of this study is the time to first severe flare as measured by the modified SELENA-SLEDAI SLE Flare Index (SFI) [68]. This index categorizes SLE flares as either “mild or moderate” or “severe” based on six variables:

- change in SLEDAI-2K score from most recent assessment to current,
- change in signs or symptoms of disease activity,
- change in prednisone (or equivalent) dose,
- use of new medication for disease activity or hospitalization,
- change in PGA score,
- hospitalization for SLE activity (severe flare only).

The modified SELENA-SLEDAI SFI requires that a patient who has a SLEDAI score  $>12$  is considered as having a severe flare only if they have one other component present. This modification was made

because participants entering the trial with high disease activity (i.e.  $\geq 11$ ) could too easily trigger a severe flare by minor increases in SLEDAI score.

Lupus flares should be treated primarily with medications listed in the section 6.5 RESCUE MEDICATION. Only in case of insufficient response to such therapies and presence of severe SLE organ manifestations, medications listed in section 6.6 PROHIBITED MEDICATION can be used. In this situation, the participant will be considered as treatment failure but will not need to be withdrawn from the study (see section 8.2 DISCONTINUATION OF STUDY TREATMENT). To ensure that the interpretability of SLE FLARE INDEX will not be impacted by prohibited medication, such patients will be included in the intention-to-treat analysis set (see section 9.3. ANALYSIS SETS), similar to patients with a dose interruption in case of adverse events.

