### 7.3.4 SLE FLARE INDEX

For this study, SLE flares will be defined as follows:

SLEDAI-2K flare is defined as at least 1 new SLEDAI-2K mild/moderate or severe flare compared with baseline as assessed using the SLEDAI flare index (SFI).

Severe SLEDAI-2K flare is defined as presence of one or more of the following:

- Increase in SLEDAI-2K score to greater than 12. If this is the only criteria met, at least one additional criterion below must also be present to be considered a severe SLEDAI-2K flare
- New/Worse SLE activity (CNS, vasculitis, nephritis, myositis, thrombocytopenia ( $< 60,000/\text{mm}^3$ ), hemolytic anemia (hemoglobin  $< 7$  g/dL or decrease in hemoglobin  $> 3$  g/dL) requiring one or more of the following: (1) increase in prednisone (or equivalent) dose to  $> 0.5$  mg/kg/day, (2) a doubling or greater of prednisone (or equivalent) dose, (3) addition of a new systemic immunosuppressant agent (cyclophosphamide, AZA, MTX, MMF, belimumab, rituximab, or other systemic immunosuppressant therapy), or (4) hospitalization for SLE activity
- Increase in prednisone (or equivalent) to  $> 0.5$  mg/kg/day for SLE activity
- New cyclophosphamide, AZA, MTX, MMF, belimumab, rituximab (or other systemic immunosuppressant therapy) for SLE activity
- Hospitalization for SLE activity
- Increase in the 0-3 VAS anchored PGA score to  $> 2.5$

Mild/moderate SLEDAI-2K flare is defined as presence of one or more of the following:

- Increase in SLEDAI-2K score of 3 points or more (but not to more than 12)
- New/worse SLE activity (discoid, photosensitive, profundus, cutaneous vasculitis, bullous lupus, nasopharyngeal ulcers, pleuritis, pericarditis, arthritis, fever due to SLE)
- Increase in prednisone (or equivalent), but not to  $> 0.5$  mg/kg/day, for SLE activity
- Added NSAID or hydroxychloroquine (or other antimalarial therapy) for SLE activity
- Increase in the 0-3 VAS anchored PGA score by  $\geq 1$ , but not to more than 2.5

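### The protocol defines the supplementary modified ITT set in two ways, and the section 9.3 version removes patients whose switch to a prohibited immunosuppressant is itself a severe-flare and new-treatment event

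*Protocol*

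**What the plan says.** **Main set.** Section 9.3 includes all enrolled patients: "In fact, the primary and secondary outcome measures are analyzed according to the intention-to-treat principle". A modified ITT analysis and a complete-case sensitivity analysis are additional.

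**Modified ITT, first definition.** In the synopsis (Analysis of efficacy), "a modified intention-to-treat analysis will be conducted excluding patients with a dose interruption due to adverse events". No other ground for exclusion is given.

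**Modified ITT, second definition.** Section 9.3 names the adverse-event interruptions and adds "or discontinuation of study treatment for other reasons, such as use of prohibited medication (see section 6.6").

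**Status of a patient who needs a prohibited drug for a flare.** Section 7.2.3 permits section 6.6 drugs narrowly: "Only in case of insufficient response to such therapies and presence of severe SLE organ manifestations". It continues: "In this situation, the participant will be considered as treatment failure but will not need to be withdrawn from the study". To keep the flare index interpretable, it then says that "such patients will be included in the intention-to-treat analysis set".

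**Flare definition.** One sufficient criterion for a severe flare in section 7.3.4 is "New cyclophosphamide, AZA, MTX, MMF, belimumab, rituximab (or other systemic immunosuppressant therapy) for SLE activity". Section 6.6 prohibits "B-cell depleting agents (e.g. rituximab, obinutuzumab or ocrelizumab") and also cyclophosphamide, so two drugs named in the flare criterion are on the prohibited list.

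**Endpoints touched.** Section 3.2.3 lists time to first flare and time to new treatments for lupus activity as secondary endpoints. Section 9.5.2 analyses both by Kaplan-Meier.

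**The concern.** Two things are at issue. First, membership of the modified ITT set depends on which section the analyst follows. A patient taken off study treatment because rituximab was started for lupus is in the set under the synopsis and out of it under section 9.3.

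Second, the section 9.3 version selects on a post-baseline event that the protocol elsewhere treats as an outcome. Dropping such a patient removes a flare and a new-treatment start from the curves meant to describe flares and new treatments. In a 10-patient study without a control arm, nothing offsets this, and one or two patients move a percentage visibly.

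A related gap affects every set. Section 7.2.3 uses the label treatment failure, but the SRI-4 definitions give it no effect. A patient rescued with a prohibited drug could be scored as an SRI-4 responder, even in the main ITT analysis.

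**Working it through.** **Step 1. The plan's own figure.** The denominator is the enrolled number. Section 9.2 needs 5 patients and assumes 50% drop-out: 5 / (1 − 0.50) = 10. This reproduces and is not in dispute. The protocol gives no flare, failure or exclusion rate, so every count below is an assumption.

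**Step 2. The same patient traced through the sections.** Take a patient whose study treatment stops in the dosing phase because a prohibited systemic immunosuppressant is started for lupus activity.

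| Place | Consequence |
|---|---|
| 7.2.3 | Treatment failure; stays in the study and in ITT |
| 7.3.4 | Severe flare by that criterion alone |
| 3.2.3, time to new treatments | Event |
| Synopsis | In the modified ITT, unless dosing was also interrupted for an adverse event |
| 9.3 | Out of the modified ITT |

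The time frame in 3.2.3 starts at baseline, so a start during dosing counts for the new-treatment endpoint. Section 9.5.2 describes that analysis over a six-month follow-up, which is one more item to align.

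**Step 3. Effect on the flare-free proportion.** Let N = 10, let r be the number flare-free, and let k be the number excluded for such a start, each of whom has flared by definition. Assume complete follow-up.

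- ITT: r / 10
- Modified ITT under 9.3: r / (10 − k)

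If only the excluded patients flare, r = 10 − k:

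- k = 1: 9/10 = 90% becomes 9/9 = 100%
- k = 2: 8/10 = 80% becomes 8/8 = 100%

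If others flare too:

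| r | ITT | k = 1 | k = 2 |
|---|---|---|---|
| 3 | 30.0% | 3/9 = 33.3% | 3/8 = 37.5% |
| 5 | 50.0% | 5/9 = 55.6% | 5/8 = 62.5% |
| 7 | 70.0% | 7/9 = 77.8% | 7/8 = 87.5% |

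Over this range the shift is about 3 to 8 points for k = 1 and 7.5 to 17.5 points for k = 2. The same arithmetic holds for freedom from new treatment.

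**Step 4. SRI-4.** Sections 3.2.3 and 7.3.3 build SRI-4 from a SLEDAI score, BILAG and the physician's global assessment, with no medication rule. Start from 5/10 = 50%:

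- the excluded patient is a non-responder: 5/9 = 55.6%
- the excluded patient is scored a responder after rescue: 4/9 = 44.4%

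The sign is not determined.

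**Step 5. The set as a whole.** Both definitions also drop adverse-event interruptions, which may remove favourable outcomes. From 5/10, dropping one failure and one responder gives 4/8 = 50.0%; dropping one failure and two responders gives 3/7 = 42.9%. The upward step in Step 3 belongs to the prohibited-drug exclusions alone, not to the net difference between the sets.

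**The case against.** The strongest reply is that this is a supplementary set in an exploratory study with no confirmatory test. ITT is the main analysis and section 7.2.3 expressly keeps these patients in it. A second set that drops discontinuations and users of prohibited drugs is a familiar per-protocol-type analysis. That stands as a limit on importance: no main flare result is affected. It does not explain why the synopsis and section 9.3 define the set differently.

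The reply also reads the exclusion closely. It is worded as discontinuation of study treatment. Treatment is eight weekly injections that may not be extended (section 6.2.4), so after the last one there is nothing to discontinue. This stands, and the exclusion should not be read as covering later flares. It still operates during dosing, where section 8.2 itself lists severe or rapidly progressive lupus as a reason to stop the study drug.

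A reader might infer more than the protocol supports:

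- **That every prohibited-drug user is a failure.** Section 6.6 also lists complementary therapies and high-potency topical steroids. Sections 7.2.3 and 7.3.4 concern treatment of lupus activity.
- **That the exclusion can only raise SRI-4 and lower SLEDAI-2K and steroid means.** Step 4 shows why this fails for SRI-4. A patient who improves on rescue also leaves the direction of the means open.
- **That section 7.2.3 has its reasoning backwards.** For time to first flare, keeping these patients in ITT is the protective choice, because the start of the drug is already an event. The sentence needs alignment with section 9.3, not reversal.

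Finally, adopting the synopsis rule would not remove all selection. Section 6.2.4 holds treatment for Grade 3 or higher toxicity whatever its cause, so a flare recorded as such an adverse event could still lead to exclusion. That is a fair caution for the redrafting. A statistical analysis plan may settle the scoring rules, but the two set definitions both stand in the protocol.

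**Conclusion.** The point holds in limited form and should be corrected. The protocol gives two definitions of the modified ITT set. The one in section 9.3 removes severe-flare and new-treatment events when study treatment is discontinued because a prohibited systemic immunosuppressant was started for lupus activity. For those two time-to-event endpoints, the upward effect of these exclusions follows from the definitions.

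Its size depends on assumed counts. With N = 10, complete follow-up and no other flares, it is 10 points for one exclusion (90% to 100%) and 20 points for two (80% to 100%). It is smaller when other patients flare as well.

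The main ITT flare analysis and the primary anti-dsDNA analysis in the ITT set are not touched. No general inflation of response rates is shown. What does reach the main analysis is the missing link between treatment failure and SRI-4, which leaves a rescued patient free to count as a responder in either set.

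**What to change.** 1. Reconcile section 9.3 and the synopsis into one modified ITT definition that does not exclude patients for starting a prohibited drug for SLE activity. The synopsis wording is the nearest existing text. State also how a dose hold caused by lupus activity is classified.
2. State for all analysis sets that starting a prohibited drug for SLE activity is a flare event and a new-treatment event on its start date, and is non-response for SRI-4 and LLDAS from then on. This gives the treatment-failure label in section 7.2.3 an analytic consequence. LLDAS needs it too: section 7.3.2 requires permitted immunosuppressants, whereas section 3.2.3 leaves that word out.
3. Align the last sentence of section 7.2.3 with section 9.3, so that both say in which sets these patients are kept and how they are counted.

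The cost is wording in the synopsis and in sections 9.3, 7.2.3 and the response definitions. No new data are needed and no treatment rule changes. The downside is that some response and modified ITT figures become slightly less favourable.
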